# Feasibility, Acceptability, and Protective Efficacy of Seasonal Malaria Chemoprevention Implementation in Nampula Province, Mozambique: Protocol for a Hybrid Effectiveness-Implementation Study

**DOI:** 10.2196/36403

**Published:** 2022-09-23

**Keywords:** malaria, chemoprevention, children, protocol, Nampula, Mozambique, feasibility, effectiveness, mixed methods, SMC, SP+AQ, hybrid effectiveness, cRCT

## Abstract

**Background:**

Seasonal malaria chemoprevention (SMC) is a highly effective community-based intervention to prevent malaria infections in areas where the malaria burden is high and transmission occurs mainly during the rainy season. In Africa, so far, SMC has been implemented in the Sahel region. Mozambique contributes 4% of the global malaria cases, and malaria is responsible for one-quarter of all deaths in the country. Based on recommendations in the Malaria Strategic Plan, the Malaria Consortium, in partnership with the National Malaria Control Programme in Mozambique, initiated a phased SMC implementation study in the northern province of Nampula. The first phase of this 2-year implementation study was conducted in 2020-2021 and focused on the feasibility and acceptability of SMC. The second phase will focus on demonstrating impact. This paper describes phase 2 of the implementation study.

**Objective:**

Specific objectives include the following: (1) to determine the effectiveness of SMC in terms of its reduction in incidence of malaria infection among children aged 3 to 59 months; (2) to determine the chemoprevention efficacy of sulfadoxine-pyrimethamine plus amodiaquine (SP+AQ) when used for SMC in Nampula Province, Mozambique, and the extent to which efficacy is impacted by drug resistance and drug concentrations; (3) to investigate the presence and change in SP+AQ– and piperaquine-resistance markers over time as a result of SMC implementation; and (4) to understand the impact of the SMC implementation model, determining the process and acceptability outcomes for the intervention.

**Methods:**

This type 2, hybrid, effectiveness-implementation study uses a convergent mixed methods approach. SMC will be implemented in four monthly cycles between December 2021 and March 2022 in four districts of Nampula Province. Phase 2 will include four components: (1) a cluster randomized controlled trial to establish confirmed malaria cases, (2) a prospective cohort to determine the chemoprevention efficacy of the antimalarials used for SMC and whether drug concentrations or resistance influence the duration of protection, (3) a resistance marker study in children aged 3 to 59 months to describe changes in resistance marker prevalence over time, and (4) a process evaluation to determine feasibility and acceptability of SMC.

**Results:**

Data collection began in mid-January 2022, and data analysis is expected to be completed by October 2022.

**Conclusions:**

This is the first effectiveness trial of SMC implemented in Mozambique. The findings from this trial will be crucial to policy change and program expansion to other suitable geographies outside of the Sahel. The chemoprevention efficacy cohort study is a unique opportunity to better understand SMC drug efficacy in this new SMC environment.

**Trial Registration:**

ClinicalTrials.gov NCT05186363; https://clinicaltrials.gov/ct2/show/NCT05186363

**International Registered Report Identifier (IRRID):**

DERR1-10.2196/36403

## Introduction

### Overview

The World Health Organization (WHO) defines seasonal malaria chemoprevention (SMC) as the intermittent administration of full treatment courses of an antimalarial medicine during the malaria season to prevent malarial illness, with the objective of maintaining therapeutic antimalarial drug concentrations in the blood throughout the period of greatest malarial risk [1-5]. It involves administering monthly courses of sulfadoxine-pyrimethamine (SP) and amodiaquine (AQ) during this peak transmission period to those most at risk: children 3 to 59 months of age [6]. SMC has been demonstrated to be a highly effective intervention that can prevent up to 75% of malaria cases in eligible children [7]. It has also been shown that the intervention can be delivered safely at scale, achieving high coverage [8,9]. To date, SMC has only been adopted and scaled up in Sahelian countries of West and Central Africa, following the WHO recommendation for this region to be the first to implement SMC. However, in many parts of East and Southern Africa, there remain concerns over widespread resistance to SP, which may reduce the effectiveness of SMC [10,11]. However, it has been suggested that SP may retain its protective efficacy even in areas where resistance is high [12,13].

Mozambique accounts for 4% of global malaria cases, and the disease is highly endemic in the entire country, with the highest prevalence in the north and along the coast [14-16]. According to surveys conducted in Mozambique, the national prevalence of malaria in children aged 6 to 59 months remained stable at 38% in 2011 [17], 40% in 2015 [18], and 39% in 2018 [19]. The prevalence varies across the country, with it being higher in the northern and central provinces and lower in the southern provinces. Nampula was one of the provinces with the highest prevalence of malaria (65%-66%) in 2015. However, a slight decrease was observed in 2018 to 48%, but it remained one of the highest prevalence rates after Cabo-Delgado (57%) [19]. Among chemoprevention strategies implemented in Mozambique, for more than 10 years, the Mozambique Ministry of Health and the National Malaria Control Programme (NMCP) have been actively implementing intermittent preventive treatment in pregnancy using SP [18].

To date, in Mozambique, studies about delivery of intermittent preventive treatment in infants (IPTi) with SP have been conducted and have been paired with the Expanded Programme on Immunization during routine contacts [20,21]. Even though different research studies about the resistance of SP in sub-Saharan Africa exist in the literature, there is no robust evidence about the impact of resistance on the efficacy of intermittent prevention treatments as an SMC strategy in the region [2,22] or IPTi in Mozambique [23]. A midterm review of the country’s Malaria Strategic Plan 2017-2022 recommended SMC as a strategy to accelerate the impact of treatment in the highest-burden locations [24]. To assess whether SMC can be an effective malaria prevention strategy in an area where resistance to SP is assumed to be high, the Malaria Consortium, in partnership with the NMCP in Mozambique, initiated a phased SMC implementation project in Nampula Province. The project was designed as a 2-year hybrid effectiveness-implementation study that took place over two consecutive phases.

### Phase 1

The first phase focused on exploring the feasibility and acceptability of SMC outside of the Sahel [25]. It was conducted between November 2020 and February 2021 and involved administering four monthly cycles of SMC to a target population of around 72,000 children in two districts of Nampula Province, Malema, and Mecubúri. SMC delivery followed the standard door-to-door delivery model commonly used in Sahelian countries, with trained volunteers acting as community distributors, supervised by health facility workers. A third district, Lalaua, where SMC was not implemented served as a control area. Research activities included the following:

Documentation of how the SMC implementation model used in the Sahel was adopted to the local context.A representative end-of-round household survey to assess coverage and quality of delivery,Interviews and focus group discussions with key stakeholders.A quality assessment of health management information system (HMIS) data on malaria indicators reported at the health facility and district levels.A nonrandomized controlled trial to estimate the ratio of the hazard of developing one or more episodes of malaria during SMC cycles among a sample of children in an intervention district compared to the hazard in the control district.A study of molecular resistance markers to determine baseline prevalence of SP and AQ resistance and any increase in resistance prevalence after one annual round of SMC [25].

While data analysis is ongoing, preliminary results suggest that SMC is a feasible and acceptable intervention and that it confers protection from malaria to eligible children. Detailed results from phase 1 will be published elsewhere.

### Phase 2

The second phase will focus on demonstrating impact by addressing feasibility and effectiveness of SMC and chemoprevention efficacy. This protocol describes phase 2 of the implementation study.

### Objectives

Phase 2 aims to test the feasibility, effectiveness, and chemoprevention efficacy of SMC with SP plus AQ (SP+AQ) in Nampula Province in Mozambique, where malaria transmission is highly seasonal. Specific objectives include the following:

To determine the effectiveness of SMC in reducing the incidence of malaria infection among children aged 3 to 59 months.To determine and measure efficacy as follows:To determine chemoprevention efficacy of SP+AQ when used for SMC in Nampula Province, Mozambique.To calculate the extent to which efficacy is impacted by drug resistance and drug concentrations.To investigate the presence and change of SP+AQ– and piperaquine-resistance markers over time as a result of SMC implementation.To understand the impact of the SMC implementation model by determining process, costing, and acceptability outcomes for the intervention.

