## Methods

### Study Design

This type 2, hybrid, effectiveness-implementation study uses a convergent mixed methods approach [26]. As the study includes components of clinical effectiveness and implementation research, a type 2, hybrid, effectiveness-implementation design was selected. These designs provide benefits over pursuing these lines of research independently; for example, they offer more rapid translational gains, more effective implementation strategies, and more useful information for decision makers. SMC will be implemented in four monthly cycles between January 2022 and April 2022 in four districts of Nampula Province (Figure 1): Malema and Mecubúri, where phase 1 of the study was conducted, will continue to receive SMC in phase 2; Lalaua, the control area in phase 1, and Muecate will receive SMC for the first time in phase 2. The research will involve the following components:

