**Figure 1 figure1:**
[figure not shown]
Intervention districts in Nampula Province, Mozambique.

Conducting a cluster randomized controlled trial (cRCT) through passive surveillance to establish confirmed malaria cases among participating children.Conducting a prospective chemoprevention efficacy cohort study to determine whether SP+AQ provides 28 days of protection from infection, and whether drug concentrations and resistance influence the duration of protection.Conducting a resistance marker study in children aged 3 to 59 months in the two research districts plus the two standard intervention districts to describe changes in resistance marker prevalence over time.Conducting a process evaluation of the SMC implementation looking at cost and process outcomes.

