### Sample Sizes

#### Cluster Randomized Controlled Trial

Clusters will be selected for the intervention arm at the community level in two districts. The study will be powered to have an 80% chance of detecting a significant reduction in RDT-confirmed malaria incidence at the 5% confidence level using a chi-square test comparing two independent proportions in a cluster randomized design. We are aiming to detect a significant reduction in malaria incidence from 0.2 to 0.12 clinical episodes per child per high-transmission season, corresponding to the SMC round. The clinical episodes should be of sufficient severity to present to a health facility, and the reduction in episodes should be equivalent to an odds ratio of 0.66, or a minimum effect size of 33%. This is based on the assumption that the efficacy of SP+AQ in Northern Mozambique, where the prevalence of resistance alleles in circulating parasites is high, is half of that found in studies in West African settings. To account for the cluster randomized design, we assumed an intracluster correlation for malaria outcomes within communities of 0.23, based on data from SMC coverage surveys conducted by the Malaria Consortium in 2020 [27] and 2021 [28]. A cluster size of 15 children per community was selected, and children in the intervention and control arms were recruited in a ratio of 1:1.5. This resulted in a total sample size of 2850 eligible children in 190 clusters: 1710 in 114 clusters in the control arm and 1140 in 76 clusters in the intervention arm. A total of 76 communities from a list of all communities will be selected as intervention districts using a simple random method. Then, 114 communities will be selected at random from among those remaining for inclusion in the control arm.

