#### Resistance Marker Study

Trends in SP and AQ resistance will be monitored in the two original intervention districts, as well as in the two research districts. Additionally, in the new phase 2 areas, the prevalence of *P*
*falciparum* plasmepsin 2 (*Pfplm2*) will be determined to inform future studies on appropriate use of dihydroartemisinin piperaquine for chemoprevention. A health facility–based, cross-sectional survey will be conducted before SMC project implementation (ie, baseline) and after one complete round of SMC distribution (ie, end line). Monitoring the prevalence of alleles associated with resistance to drugs is, by standard protocol, performed by collecting samples from symptomatic children with evidence of infection. The sample collection will be performed in four selected health facilities in each study district. The key markers to be monitored are as follows: *Pfdhfr*—codons 51, 59, 108, and 164; *Pfdhps*—codons 431, 437, 540, 581, and 613; *Pfcrt*—codons 72 to 76; *pfmdr1*—codons 86, 184, and 1246; and *Pfplm2*.

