#### Resistance Marker Study

Prevalence of *Pfdhps*, *Pfdhfr,*
*Pfcrt*, and *Pfmdr1* alleles in parasites obtained from participating children will be ascertained. Copy numbers of *Pfplm2* will also be quantified.

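### Objective 3 attributes resistance-marker change to SMC, but the marker component is an uncontrolled before-after survey whose phase 2 baseline already follows one SMC round in two districts

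*Protocol article*

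**What the plan says.** - **Aim, Objectives section (and abstract).** The third objective concerns change in "piperaquine-resistance markers over time as a result of SMC implementation". This is causal wording.
- **Aim, Study Design section, list of components.** The same component is there "to describe changes in resistance marker prevalence over time". This is descriptive wording.
- **Survey, Recruitment and Data Collection, Resistance Marker Study.** A cross-sectional "survey will be conducted before SMC project implementation (ie, baseline) and after one complete round of SMC distribution (ie, end line"). Symptomatic children with evidence of infection are sampled at four facilities in each of four districts.
- **Analysis, Data Analysis, Resistance Marker Study.** Prevalence of the listed "alleles in parasites obtained from participating children will be ascertained", and *Pfplm2* copy number is quantified. No comparator is named.
- **SMC history, Study Design.** Malema and Mecubúri are the districts "where phase 1 of the study was conducted, will continue to receive SMC in phase 2". The Phase 1 section says that phase 1 comprised four monthly cycles.
- **Randomisation, Sample Sizes, Cluster Randomized Controlled Trial.** In Lalaua and Muecate, 76 communities are drawn for intervention, then "114 communities will be selected at random from among those remaining for inclusion in the control arm".
- **Earlier marker data, Phase 1 section.** Phase 1 included a marker study to "determine baseline prevalence of SP and AQ resistance and any increase in resistance prevalence after one annual round of SMC". Its districts are not named.

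**The concern.** An objective phrased as the result of SMC invites a causal conclusion, and the survey supplies only a difference between two dates. Three things make that difference hard to read:

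1. Background or seasonal movement in marker prevalence is inseparable from any effect of SMC.
2. The survey is described as preceding implementation, which is untrue of two of the four districts.
3. In the other two districts, facility attendees may come from communities with and without SMC.

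The error can go either way. A flat result could be reported as reassurance that SMC does not select for resistance, or a background rise could be blamed on SMC. The Discussion already summarises phase 1 as showing no apparent harm to the resistance profile after one annual round, and says the present findings are meant to inform national and global policy.

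**Working it through.** **1. The plan's own figures.** The sample total reproduces: 3 × 300 + 600 = 1500, or 750 per survey. The 90% power for a rise from below 1% to 2%, with 150 children per survey, does not. I used the pooled two-proportion test at two-sided 5% (sidedness is not stated):

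power = Φ[(p₂ − p₁ − 1.96·SE₀)/SE₁]

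SE₀ uses the pooled proportion and SE₁ the two separate proportions. For 150 v 150 and 1% v 2%, SE₀ = 0.01404 and SE₁ = 0.01402, so power = Φ(−1.25) = 10.6%. For lower starting prevalences it is 21% (0.5%), 36% (0.1%) and 41% (0.01%). That is a separate matter. It shows here that the before-after contrast is itself imprecise, apart from being uncontrolled.

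**2. What the before-after difference identifies.** In each district, observed change = background and seasonal change + effect of SMC. There is one observed quantity and two unknowns. More children narrow the interval around the sum and do not separate its parts.

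**3. What the phase 2 baseline is, by district.**

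| District | SMC in phase 1 | Phase 2 baseline |
|---|---|---|
| Malema, Mecubúri | Yes, four cycles | After one annual round |
| Lalaua, Muecate | No | Before SMC, if the survey precedes the first cycle |

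For the second row, the abstract dates the cycles December 2021 to March 2022 and Study Design January to April 2022, while data collection began in mid-January 2022. These dates need reconciling. I draw no further conclusion from them.

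**4. Mixing of arms in Lalaua and Muecate.** If a true shift Δ occurs only in SMC communities, a mixed end-line sample shows s·Δ, where s is the share of sampled cases from those communities. Let c be the fraction of the catchment living in SMC communities. With the planned incidences of 0.20 and 0.12 (ratio 0.6):

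s = 0.6c / (0.6c + 1 − c)

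The article gives no c, so these values are assumptions:

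- c = 0.1: 0.06/0.96 = 6%
- c = 0.4 (76/190, which counts trial clusters only): 0.24/0.84 = 29%
- c = 0.8: 0.48/0.68 = 71%

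The dilution factor could therefore lie almost anywhere.

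**5. What a by-arm comparison could show.** End-line children in the two districts number 300 + 150 = 450. Assume first that every child can be assigned to a trial community, with no clustering, and compare 1% with 2%.

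- Split 180:270 (40:60 by clusters): SE₀ = 0.01131, SE₁ = 0.01207, power = Φ(−1.01) = 15.7%.
- Split 129:321 (weighted by expected cases): 16.8%.
- With design effect 1 + (450/190 − 1) × 0.23 = 1.31: 13.3% and 14.5%. The 0.23 is the plan's value for malaria outcomes; using it for markers is an assumption.
- If only half the children can be assigned (assumption): 10% to 12%.
- Comparing arms on change from baseline, with unpooled variances: 9.5% (40:60) and 8.5% (29:71).

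For comparison, 450 v 450 before-after gives 23.4%. Against 1% in the control arm, the smallest intervention-arm prevalence detectable with 90% power is about 7% to 9% using all 450 children.

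**The case against.** The strongest reply is that this is a matter of wording. Study Design already states a descriptive aim. The analysis text is a two-sentence condensation of a fuller protocol that, with its data collection tools, is held separately. Recording of residence and analysis by arm may be specified there, so their absence from the article is not an omission. That stands, and I do not count it as one. What remains is that the article states two different aims for one component and misdescribes the baseline in two districts.

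Three stronger readings are tempting and are not supported.

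- **No pre-SMC data exist for Malema and Mecubúri.** A reader might infer this, but phase 1 had its own marker study with a baseline. The statement holds only for the phase 2 survey. Whether the phase 1 study covered both districts is not stated.
- **Comparing by randomised arm is free and would deliver the causal answer.** It needs residence recorded, loses children from non-trial communities, exists in two of four districts and has low power. It also compares arms only among symptomatic infected children, a group that SMC itself alters after randomisation. Breakthrough cases under SMC could be enriched for resistant parasites without any change in the wider parasite population. Movement of parasites between neighbouring communities would blur the arms.
- **A definite dilution, such as a 10-point shift appearing as about 3.** This takes 76/190 as the SMC share among facility attendees. Facility catchments, the total number of communities and the SMC status of unselected communities are not given.

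**Conclusion.** The point holds in a limited form. On the text alone, objective 3 claims more than its survey can support and conflicts with the component's own description. The before-implementation label is wrong for two of the four districts. Mixing of arms in the other two is probable, but it is an inference from community randomisation combined with facility sampling, and its size cannot be fixed (6% to 71% of cases from SMC communities over the assumed range). A by-arm display is worth having because it is concurrent and follows the randomised allocation. With about 16% power for 1% v 2% under favourable assumptions, and conditioning on being a case, it cannot by itself establish an effect of SMC on resistance.

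**What to change.** 1. Reword objective 3, in the abstract and the Objectives section, to match the descriptive aim in Study Design. Report before-after results as change over time, not as an effect of SMC.
2. Label the Malema and Mecubúri phase 2 baseline as following one round. Use the phase 1 pre-SMC marker survey as the reference where it covered those districts, after confirming which districts it sampled.
3. If community of residence is recorded, show Lalaua and Muecate marker prevalence by randomised arm as exploratory, with confidence intervals. State that only symptomatic infected children are compared.

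**Cost.** Items 1 and 2 change wording and labels; item 2 also needs access to the phase 1 data. Item 3 needs one field on the survey form and one added analysis, with no extra samples, and brings the loss of children and low power shown above. The article reports that data collection ended in mid-June 2022. If residence was not captured, item 3 falls away and items 1 and 2 still apply.

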## Methods

### Study Design

This type 2, hybrid, effectiveness-implementation study uses a convergent mixed methods approach [26]. As the study includes components of clinical effectiveness and implementation research, a type 2, hybrid, effectiveness-implementation design was selected. These designs provide benefits over pursuing these lines of research independently; for example, they offer more rapid translational gains, more effective implementation strategies, and more useful information for decision makers. SMC will be implemented in four monthly cycles between January 2022 and April 2022 in four districts of Nampula Province (Figure 1): Malema and Mecubúri, where phase 1 of the study was conducted, will continue to receive SMC in phase 2; Lalaua, the control area in phase 1, and Muecate will receive SMC for the first time in phase 2. The research will involve the following components:

